### Laboratory procedures

#### Serology

Two different anti–*T. cruzi* serologic tests based on different antigens were used for assessing patient eligibility. To avoid interlaboratory variability, serum samples collected at the times indicated in the protocol will be sent at the end of the study to a centralized laboratory that will process them using two techniques in parallel: Architect Chagas (Abbott Laboratories, Wiesbaden, Germany) and ORTHO *Trypanosoma cruzi* ELISA Test System (Ortho Clinical Diagnostics, Raritan, NJ, USA). In order to give greater robustness to the results, samples from external quality control sent by the National Program of Quality Control of Brazil will be included.

#### PCR

Laboratories included in the project will carry out the same reverse transcriptase (RT)-PCR protocol following the instructions included in the laboratory manual agreed among all of them. To carry out this technique, 5 ml of whole blood will be collected and mixed with 5 ml of guanidine hydrochloride 6 M–ethylenediaminetetraacetic acid 0.2 M for a minimum of 72 h at room temperature. Three DNA extractions will be performed using the manual column method (High Pure PCR Template Preparation Kit; Roche Diagnostics, Mannheim, Germany), except in Spanish centers (Vall d´Hebron University Hospital and Ramón y Cajal University Hospital) where DNA extraction will also be done in triplicate using an automated extraction method (NucliSens easyMAG, bioMèrieux, Marcy l’Etoile, France).The consensual PCR protocol consists of a real-time multiple PCR (Duffy et al. 2013) [30] that allows the amplification of a *T. cruzi* satellite DNA region and a linearized recombinant plasmid used as an internal amplification control. The RT-PCR will be carried out in duplicate from each of the extractions. At least one amplification of the six performed with an amplification cycle (cycle threshold) of *T. cruzi* below 40 and a correct value of Internal Amplification Control (IAC) will be interpreted as positive. To be correct, the values of the IAC must meet Tukey’s criteria.

To assess the homogeneity of the results obtained by the different laboratories, a harmonization panel consisting of ten tubes containing blood with uninfected guanidine and infected with 1, 10, and 100 parasitic equivalents per milliliter of *T. cruzi* strains TcV and TcVI was processed. The samples were processed blindly by the different laboratories, and the results were evaluated by an external center in charge of providing the panel and analyzing the results (Instituto de Investigaciones en Ingeniería Genética y Biología Molecular, Buenos Aires, Argentina). On the other hand, and following the same work scheme, four external quality control panels will be analyzed during the study period.

#### HLA typing

The typing of HLA-B alleles is carried out from the dried blood samples on paper (dried blood spots [DBS]). For this purpose, DNA is extracted using DNA Elution Solution reagent (catalog no. 159994; Qiagen, Carpinteria, CA, USA), and the concentration and quality are evaluated by measuring the absorbance at 260 and 280 nm using the Colibri microvolume spectrometer (Titertek-Berthold, Pforzheim, Germany). The characterization of the HLA-B alleles is carried out by PCR sequence-specific oligonucleotide (SSO) (Luminex Corp., Austin, TX, USA), following the instructions of the Lifecodes HLA typing kit (Immucor; Diagnóstica Longwood, Zaragoza, Spain). Briefly, the PCR-SSO/Luminex consists of amplification with biotinylated primers of the most polymorphic regions of the HLA-B gene, followed by hybridization of the amplified product with specific probes for each allele located on the surface of Luminex microspheres and revealed with conjugated streptavidin with phycoerythrin. Finally, it is analyzed using an xMAP100 fluoroanalyzer (Luminex Corp.).

#### BNZ serum concentration

Quantification of BNZ is done from dried blood samples on paper (DBS). The quantification is performed by liquid chromatography (ACQUITY ultra performance liquid chromatography high-strength silica T3 C18, 2.1 × 50 mm; Waters, Milford, MA, USA) coupled to triple-quadrupole mass spectrophotometry (Xevo TQ; Waters).

### Study organization

The MULTIBENZ study network includes four countries and seven centers, with the Spanish coordinating center located at Vall d’Hebron University Hospital in Barcelona, Spain. The study contemplates a total of three stages, which are outlined below.
**Recruitment sites**

Countries involved in the recruitment will be Spain (University Hospital Vall d’Hebron, Barcelona; University Hospital Ramón y Cajal, Madrid), Argentina (Instituto Nacional de Parasitología [name] Chaben, Buenos Aires; Instituto de Cardiología Juana Francisca Cabral, Corrientes), Brazil (Centro de Pesquisas René Rachou – Fundação Oswaldo Cruz, Belo Horizonte; Hospital Universitário Clemente de Faria, Montes Claros), and Colombia (Fundación Cardioinfantil – Instituto de Cardiología).
2.**Selection phase**

Patients with CD in the chronic phase who come to the study centers will be evaluated in order to assess if they meet the inclusion criteria. For those who agree to participate and sign the informed consent, detection of parasitic DNA by PCR in peripheral blood will be performed. Patients with a PCR result negative for *T. cruzi* will be withdrawn from the study. The screening procedure must occur up to 90 days or less before the initiation of treatment. Serology and DNA determination by PCR will be accepted as valid and will not need to be repeated if a positive result was obtained in a previous period of 3 months.

All patients will undergo a clinical history and physical examination. Peripheral blood extraction will be performed for analysis: hemogram, biochemistry assays, and HLA study, and a negative pregnancy test (either in urine or blood) is mandatory in case of women in childbearing age. The evaluation of the visceral involvement of CD will be completed with a chest x-ray and electrocardiogram. The performance of other complementary tests will be carried out according to the clinical investigator’s decision, but they will not be considered necessary for the inclusion of the patient.
3.**Treatment phase**

In this phase, the patient will be randomized to one of the three arms of treatment, whose duration will be 60 days independently of the arm assigned. Initially, a baseline visit will be performed in which the patient will be trained on how to take the drug and identify AEs. After that, a total of four scheduled visits will occur during the treatment period, at 7, 15, 28, and 60 days after treatment initiation. A summary of these visits is presented in Table 3.

**Table 3 Tab3:** Visit schedule

	Selection visit (from − 3 months to day 0)	Baseline visit (day 0)	Treatment visit (day 7 ± 2)	Treatment visit (day 15 ± 3)	Treatment visit (day 28 ± 4)	End of treatment visit (day 60 ± 7)	Side effect visit (not scheduled)	Follow-up visit (months 4, 6, and 8)	Final visit (month 12)
**Informed consent**	x								
**Demographic data**	x								
**Pathological background**	x								
**Toxic habits**	x								
**Chagas disease history**	x								
**Concomitant medication**	x	x	x	x	x	x	x	x	x
**Directed anamnesis**	x	x	x	x	x	x	x	x	x
**Physical examination**	x	x	x	x	x	x	x	x	x
**Pregnancy test**		x							
**Hematology**	x		x	x	x	x	x		
**Biochemistry**	x		x	x	x	x	x		
**HLA**	x								
**Chest x-ray**	x								
**EKG**	x								
**PK**				x		x	x		
**Serology**	x								x
**PCR**	x		x	x	x	x		x	x
**Other complementary tests**	x								
**Adverse events**		x	x	x	x	x	x		
**Randomization**	x								
**Study medication**		x	x	x	x	x			

*Abbreviations: EKG* Electrocardiogram, *HLA* Human leukocyte antigen, *PCR* Polymerase chain reaction, *PK* Pharmacokinetics

During this phase, any patient may consult spontaneously for the eventual occurrence of any AE. The decision to interrupt the treatment will be according to the discretion of the clinical researcher treating the patient, taking into account the severity, intensity, and extent of these AEs. In addition, the patient may decide unilaterally to suspend or not the medication at any time during the treatment period.
4.**Follow-up phase**

Once the patient has taken the last dose of treatment, which may be at the end of the therapeutic scheme (day 60), when a severe AE that obliges the patient to suspend the medication occurs, or when the patient unilaterally decides to suspend the medication, this phase will begin, and it will last up to 12 months after randomization. The visit schedule of this phase is presented in Table 3.

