Currently, there are only two available drugs to treat CD: nifurtimox and benznidazole (BNZ). Of these two, BNZ is the one most studied and most often used as a treatment. However, current schemes of this treatment have some limitations. On the one hand, it has a limited efficacy based on seroconversion (around 50–80% in the acute phase of the disease and 8–20% in the chronic phase) [7]. Another important limitation is the high rate of adverse events (AEs) when using these drugs. The incidence of AEs related to BNZ varies from 40–50% up to 98%, and around 15% of these patients have to definitively stop the treatment for this reason, with the rate even higher in patients treated with nifurtimox [8–10]. The most commonly observed AEs are hypersensitivity (rash, fever, generalized edema, lymphadenopathy, myalgia, and arthralgia), gastrointestinal disorders, bone marrow toxicity (neutropenia and thrombocytopenic purpura), and peripheral polyneuropathy [9]. Current knowledge about the BNZ toxicity mechanisms is scarce because the main studies have focused on the clinical aspects of these AEs [10]. Our group recently carried out an analysis of the cytokine profile and human leukocyte antigen (HLA) classes I and II of patients who were treated with BNZ, and we found a higher treatment discontinuation rate due to skin hypersensitivity AEs in patients who had the HLA-B*3505 allele [11].

Moreover, another drawback of the studies assessing the efficacy of BNZ in chronic CD is the lack of a biomarker to define the cure of disease. Currently, the cure criteria are negative seroconversion of two serologic assays against different antigens, but it usually takes several years after an effective treatment, precluding its use in clinical trials. In addition, detection of *T. cruzi* DNA in peripheral blood cannot be used to define cure, because a negative result does not mean absence of the infection; however, in recent years, it has become an important tool used to identify therapeutic failure when the result remains positive after completed treatment [8].

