• Having laboratory parameters outside the range of normal or that are considered clinically relevant by the responsible physician: ◦ Total leukocyte count must be within the normal range, with an acceptable range of ± 5%. ◦ Total platelet count must be within the normal range up to 550,000/mm^3^ or 550 × 10^9^/L. ◦ Total bilirubin must be within the normal range. ◦ Transaminase levels must be within the normal range, with an acceptable range of 25% above the upper limit of normal (ULN). ◦ Total creatinine level must be within the normal range, with an acceptable variation of 10% above the ULN. ◦ Alkaline phosphatase level must be within the normal range up to < 2.5× ULN. ◦ Gamma glutamyl transferase level must be within the normal range up to 2× ULN. ◦ Fasting glucose must be within the normal range.	

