### Randomization and follow-up

Patients are randomly assigned to receive BNZ 150 mg/day for 60 days, 400 mg/day for 15 days, or the standard scheme of 300 mg/day for 60 days. Because this is a double-blind trial, investigators and all sponsor staff will not be aware of the treatment allocation and randomization list until the end of the trial. Double-blinding will be adopted for all trial arms. Patients will be randomized 1:1:1, and randomization will be done via a remote and interactive response system, according to a predefined list. To avoid bias, randomization will be centralized and concealed. The treatment groups will be allocated on day 1 on the basis of a balanced block randomization, taking into account the country. Each patient will be assigned an identification code that will correspond to the trial kit number allocated to the patient. The label will indicate the trial number and the number of the kit, but it will not indicate the treatment designation.

Scheduled follow-up visits will occur at 7, 15, 28, and 60 days and up to 4, 6, 8, and 12 months after initiation of treatment. More information is provided in Fig. 1.

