Safety laboratory parameters (hematology and biochemistry) will also be described individually per trial arm, showing the proportion of patients by degree of elevation relative to upper limit of normal and baseline values, as well as blood level changes over time.

Safety data will be correlated to efficacy and treatment compliance data and to PK parameters. Differences in the rate of absorption in serology will be estimated with *t* test pairs or the Wilcoxon test, depending on their distribution. All safety analyses will be carried out on all patients treated, understood as all patients who receive at least one dose of treatment. Finally, the sensitivity, specificity, and positive and negative predictive values of the presence of HLA-B*3505 and their relationship with the occurrence of SAEs will be calculated.

The efficacy analysis will be carried out according to the intention-to-treat principle. The group of patients analyzed will be all randomized patients in each of the treatment branches. Cases lost during follow-up and dropouts will be considered treatment failures.In addition, a per-protocol analysis will be defined as all patients receiving randomized treatment who meet the main criteria, have not permanently left the administration of the treatment, and have no other protocol deviation. Patients lost to follow-up will be excluded unless they present a positive PCR result, in which case, they will be included in the analysis. The results will be analyzed using IBM SPSS Statistics version 19.0 software (IBM Corp., Armonk, NY, USA).

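### The only scheduled blood count and chemistry before dosing may be up to 90 days old at first dose, so laboratory eligibility and the laboratory baseline can be out of date (minor)

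*Protocol article*

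**What the plan says.** Under Study organization, the selection-phase text gives a single limit for the whole of screening: "The screening procedure must occur up to 90 days or less before the initiation of treatment". The safety bloods are part of that phase: "Peripheral blood extraction will be performed for analysis: hemogram, biochemistry assays, and HLA study". A validity rule for existing results is stated for two tests only: "Serology and DNA determination by PCR will be accepted as valid and will not need to be repeated if a positive result was obtained" within the preceding 3 months. No separate limit is given for blood counts or chemistry.

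Table 3 agrees. The hematology and biochemistry rows are marked at the selection visit (3 months before to day 0), blank at the day 0 baseline visit, and then marked at days 7 ± 2, 15 ± 3, 28 ± 4 and 60 ± 7 and at unscheduled side-effect visits. The day 0 column is otherwise used: it carries concomitant medication, anamnesis, physical examination, a pregnancy test, adverse events and study medication.

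These bloods have two uses. Table 2 applies them as entry limits, for example "Total leukocyte count must be within the normal range, with an acceptable range of" ± 5%, with further limits for platelets, bilirubin, transaminases, creatinine, alkaline phosphatase, gamma glutamyl transferase and fasting glucose. The section Sample size and data analysis then describes laboratory safety by arm, "showing the proportion of patients by degree of elevation relative to upper limit of normal and baseline values", and as change over time.

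**The concern.** A 3-month window suits serology and PCR, which here confirm a chronic infection. Blood counts and chemistry can change within weeks, and the Table 2 limits are tight: bilirubin and fasting glucose have no tolerance beyond normal, and creatinine may exceed the upper limit by only 10%. Limits that narrow lose part of their purpose if the sample may be three months old.

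Two things are at stake. The first is safety at entry. The Introduction lists "bone marrow toxicity (neutropenia and thrombocytopenic purpura" among the known toxicities of benznidazole. A silent fall in counts or rise in transaminases after selection would not reliably show in the history and examination repeated at day 0, so a patient who no longer meets the limits could be dosed. The second is attribution. Adverse events are recorded from day 0, and an abnormality first seen at day 7 is hard to date to before or after the first dose when the comparison value is months old. Values described relative to baseline then mix drift before treatment with change on treatment.

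**Working it through.** **Inputs**
- Maximum age of the screening sample at first dose: 90 days (Study organization, selection phase). Table 3 gives the same limit as 3 months.
- Scheduled hematology and biochemistry before dosing: one, at selection (Table 3).
- First on-treatment draw: day 7 ± 2, that is day 5 to day 9 (Table 3).
- First dose taken as day 0, where Table 3 first marks study medication.

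**Formula**

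Age of the last pre-dose sample at the first on-treatment draw = age at first dose + 5 to 9 days.

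**As written.** At the ceiling: 90 + 5 = 95 days to 90 + 9 = 99 days.

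**With a shorter limit for the safety bloods.** The window lengths are assumptions; the article gives none.

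| Maximum age at first dose (days) | Maximum age at the day 7 ± 2 draw (days) |
|---|---|
| 90 (as written) | 95 to 99 |
| 42 | 47 to 51 |
| 28 | 33 to 37 |
| 21 | 26 to 30 |
| 14 | 19 to 23 |
| 0 (day 0 draw) | 5 to 9 |

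A 28-day limit would lower the maximum age at first dose by 90 − 28 = 62 days, or 62/90 = 69%. That percentage follows from the window chosen. It measures sample age and says nothing about how many patients would be classified differently.

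**What the sample age does not touch.** The primary endpoint is sustained negative qualitative PCR, and no blood count or chemistry value enters it. Elevation relative to the upper limit of normal uses no baseline. Only the entry limits and the descriptions relative to baseline depend on the selection sample.

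**What cannot be computed.** The article gives no distribution of sample age and no within-person variation for these tests, so no number of patients wrongly dosed or misclassified can be derived.

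**The case against.** The strongest reply is that nothing here is misstated or contradictory. The text and Table 3 agree, 90 days is a ceiling, and the selection window runs up to day 0, so same-day bloods are allowed. The selection-phase text mentions PCR first and the bloods afterwards, which may mean that sites already draw them after a positive PCR. Clinical checks are repeated at day 0, and bloods follow at days 7, 15, 28 and 60. Patients with interfering liver or kidney disease are excluded. Drift before treatment should balance across randomized, blinded arms, and the laboratory tables are descriptive. A condensed article may also leave a shorter limit to the full protocol.

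Most of this stands and keeps the point minor. It does not remove it. The article prints a full visit schedule with the day 0 column filled selectively, so the blank cells are a stated schedule. The order of sentences does not fix the order of the draws. Investigators may repeat the bloods, but nothing shown requires it.

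A reader might also infer that the short arm is specially exposed, given the regimens "400 mg/day for 15 days, or the standard scheme of 300 mg/day for 60 days". If active drug starts at day 0 and is given first, 5 to 9 of 15 active days (33 to 60%) precede the day 7 draw, against 5 to 9 of 60 (8 to 15%) in the other arms. That contrast comes mostly from the denominators. The amounts taken are 2,000 to 3,600 mg at 400 mg/day and 1,500 to 2,700 mg at 300 mg/day, a ratio of 400/300 = 1.33 over the same days. The Higher dose section cites no relation between serum concentration and adverse events, and no higher proportion of side effects at 400 mg daily. A fresher pre-dose sample would not alter exposure before day 7 in any case. The documents do not support a special claim for that arm.

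**Conclusion.** The point holds as a minor, inexpensive improvement. As scheduled, the only planned hematology and biochemistry before dosing can be up to 90 days old at first dose, and 95 to 99 days old at the first on-treatment draw. Both the Table 2 limits and the laboratory baseline can therefore be out of date, for a drug with named marrow toxicity. This assumes that day 0 is the first dose and that no unscheduled repeat is done.

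Two stronger readings should be resisted. A reader might conclude that ineligible patients will be dosed in some number, but the article gives nothing from which to estimate one. A reader might also conclude that the efficacy result is at risk, but the PCR comparison does not use these values, and the sample size, type I error and power are unchanged.

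**What to change.** Keep the 3-month window for serology and PCR. For hematology and biochemistry, amend the selection-phase text and Table 3 in one of these ways:

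1. Draw them after the positive PCR result and close to dosing; or
2. Repeat them if they are older than a short window that the sponsor sets, with the result available before randomization. About 4 weeks is a reasonable starting value, but it is an assumption. It must be checked against PCR turnaround, which the article does not give; the 72-hour sample step under Laboratory procedures is only a minimum for one part of it.
3. At the least, add a pre-dose draw at the existing day 0 visit. It improves the baseline without waiting for the result, but it checks eligibility only if the result is back before randomization.

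In every case, define the laboratory baseline as the latest value before the first dose.

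**Cost.** Option 1 re-times a draw already planned. Option 2 adds a routine panel for those of the 240 patients whose sample is too old, with a possible extra contact or short delay. Some late screen failures will follow, a few from ordinary variation because several limits allow little or no margin. If results are read before randomization, these patients stay out of the intention-to-treat set. Option 3 adds one sample and no delay. Recruitment began in April 2018, so a change helps only patients still to be enrolled.

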#### Primary endpoints

The primary endpoint is parasitologic response, defined as maintained negative qualitative PCR results during the 12-month follow-up period. For efficacy assessments, the end of treatment of each treatment arm will be defined in accordance with the duration of the treatment regimen. Incidence and severity of AEs and those leading to treatment discontinuation will also be recorded.

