#### Secondary endpoints

Secondary endpoints are parasitic clearance at weeks 1, 2, 4, and 8 during the treatment period and at 4, 6, and 8 months during the follow-up period, measured by qualitative PCR. Serological response will be assessed by conventional serology at 12-month follow-up. The proportion of HLA-B*3505 carriers among the patients who experience SAEs will be recorded, as will blood concentrations of BNZ at 15 d and by the end of treatment.

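### The waiver of repeat selection tests is not limited to eligibility, so some patients may have no comparable baseline serum for the paired serology analysis

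*Protocol article*

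**What the plan says.** All references are to the protocol article.

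- **Waiver (Study organization, selection phase).** "Serology and DNA determination by PCR will be accepted as valid and will not need to be repeated if a positive result was obtained" in the 3 months before. No laboratory, assay or stored sample is specified.
- **Selection blood draw (same section).** "Peripheral blood extraction will be performed for analysis: hemogram, biochemistry assays, and HLA study". Serum for serology and blood for PCR are not in this list.
- **Schedule (Table 3).** Serology is marked at selection and at month 12 only. PCR is marked at selection and then from day 7 onward. Neither is marked on day 0.
- **Eligibility serology (Serology; Patient eligibility).** Two "serologic tests based on different antigens were used for assessing patient eligibility". Immunofluorescence, hemagglutination and ELISA all qualify.
- **Central serology (Serology).** To limit variation between laboratories, "serum samples collected at the times indicated in the protocol will be sent at the end of the study to a centralized laboratory", where two named commercial assays are run in parallel.
- **Serology endpoint and analysis.** "Serological response will be assessed by conventional serology at 12-month follow-up" (Secondary endpoints). "Differences in the rate of absorption in serology will be estimated with" a paired t test or a Wilcoxon test (Sample size and data analysis). I read the rate of absorption as assay absorbance.
- **PCR method (PCR).** "Laboratories included in the project will carry out the same reverse transcriptase (RT)-PCR protocol", with three extractions, each amplified in duplicate. The waiver is not tied to this method.

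**The concern.** The selection tests do two jobs. They establish that the patient is infected and PCR-positive, and they are the only scheduled pre-treatment serology and PCR measurements. For the first job, accepting a recent positive result is reasonable. The waiver is worded as if that were the only job.

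A paired test needs two values per patient on the same scale. The later value comes from the central assays at month 12. For a patient who used the waiver, the earlier value may be absent, or it may exist only as a local result, possibly from a method that gives no comparable absorbance. The pair is then lost, or a local reading is set against a central one. The second option brings back the inter-laboratory variation that central testing is meant to remove.

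The loss is permanent. Serum not drawn before the first dose cannot be recovered by any later analysis plan.

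There is a smaller parallel issue for PCR. Entry positivity may rest on an assay outside the harmonised protocol, and a pre-treatment sample for typing the parasite, which is a stated secondary objective, may be lacking in some patients.

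**Working it through.** **1. Patients per arm.** The article gives 240 patients, randomised 1:1:1, so 240 / 3 = 80 per arm. This figure reproduces. With 40% failures in the standard arm, halved to 20%, two-sided alpha 0.05 and 80% power:

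- Unpooled variance: n = (1.960 + 0.842)² × (0.40×0.60 + 0.20×0.80) / 0.20² = 7.849 × 0.40 / 0.04 = 78.5, so 79 per arm and 237 in total.
- Pooled variance: 82 per arm and 246 in total.

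Both are within 3% of 240. The calculation concerns the primary endpoint, so it only supplies the 80 used below.

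**2. Pairs lost.** Let w be the share of patients who use the waiver and have no banked pre-dose serum. The article does not give w, so I assume 0% to 50%. Other dropout is ignored.

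- Pairs per arm = 80 × (1 − w)
- Inflation of the standard error = 1 / √(1 − w)
- Within-arm change detectable with 80% power at two-sided 0.05, in SDs of the change = (1.960 + 0.842) / √(pairs)

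| w (assumed) | Patients without a pair, of 240 | Pairs per arm | SE factor | Detectable change (SD) |
|---|---|---|---|---|
| 0% | 0 | 80 | 1.00 | 0.31 |
| 10% | 24 | 72 | 1.05 | 0.33 |
| 20% | 48 | 64 | 1.12 | 0.35 |
| 30% | 72 | 56 | 1.20 | 0.37 |
| 50% | 120 | 40 | 1.41 | 0.44 |

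**3. Local results substituted.** Suppose all 80 pairs are kept, but a share w use a local baseline that differs from the central assay by an offset b. I assume b = 0.5 SD of the change; the documents give no value.

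- Shift in mean change = w × b
- SD of the mixture = √(1 + w(1 − w)b²)
- Test shift = w × b × √80 / SD of the mixture

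At w = 10%: the shift is 0.05, the SD is √1.0225 = 1.011, and the test shift is 0.05 × 8.944 / 1.011 = 0.44. The false-positive rate of the within-arm test is about 7% instead of 5%.

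At w = 50%: the shift is 0.25, the SD is √1.0625 = 1.031, and the test shift is 0.25 × 8.944 / 1.031 = 2.17. The false-positive rate is about 58%.

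**4. Comparison between arms.** The waiver is used at selection and allocation is concealed, so w should not depend on arm. The expected shift w × b is then the same in each arm and cancels. What remains is lost precision.

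**5. Primary endpoint.** "The primary endpoint is parasitologic response, defined as maintained negative qualitative PCR results during the 12-month follow-up period". It is qualitative and contains no change from baseline. The efficacy set is all randomised patients, so the comparison keeps 80 per arm whatever w is.

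**The case against.** The strongest reply is that the sentence excuses repeating a test and does not forbid drawing a sample. It stands in a paragraph about eligibility. The serology section separates eligibility tests from the scheduled sera sent to the central laboratory, and Table 3 marks both tests at selection for everyone, with no exception. The list of uses for the selection draw omits serology for all patients, so it is not exhaustive. The 3-month limit matches the selection window, so some accepted results may come from the trial's own centres. The full protocol and the laboratory manual are not shown and may require banking.

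Much of this stands. A missing baseline is a risk the wording leaves open; it is not a stated consequence. The reply does not close the gap, however. A site that follows the sentence literally can omit the only scheduled pre-treatment serology, and nothing in the article says that serum is still kept.

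Two stronger readings should be set aside.

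- A reader might infer that patients using the waiver drop out of the parasite analyses. The PCR outcomes are qualitative results after treatment starts and time to first positive PCR. No paired parasite analysis is described.
- A reader might infer that typing would be missing in every sustained responder who used the waiver. PCR blood is also taken on days 7, 15, 28 and 60, and an early on-treatment positive could be typed. The article states no sampling time for typing. Failures also include discontinuations for adverse events and losses to follow-up, so failing is not the same as having typeable DNA.

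**Conclusion.** The point holds for serology, as an avoidable risk to a secondary endpoint. As written, the waiver can leave patients without a baseline comparable with the central month-12 result, and the planned paired test needs one.

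The size depends entirely on the unstated waiver share, and it is zero if every site banks serum anyway. At an assumed 10% to 50%, pairs per arm fall from 80 to between 72 and 40, and the detectable within-arm change rises from 0.31 SD to between 0.33 and 0.44 SD. If local results were substituted, the within-arm change would be biased. The 7% and 58% false-positive rates illustrate this under an assumed 0.5 SD offset; they are not forecasts. Comparisons between arms would mainly lose precision.

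Non-harmonised entry PCR and a missing pre-treatment sample for typing are lesser risks. The documents do not support any claim that the primary comparison loses patients.

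**What to change.** In the selection-phase text, limit the waiver to eligibility. Suggested wording: *A positive serology or PCR result from the previous 3 months may be used to establish eligibility. A serum sample and a guanidine-EDTA blood sample are nevertheless collected from every patient before the first dose. The serum is stored for the central assays and is the only baseline used for the serology analysis.*

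The samples can be taken in the existing selection draw or on day 0 before dosing; if day 0 is used, mark it in Table 3. The same section withdraws PCR-negative patients, so the text should also say whether a negative trial PCR on this sample affects a patient admitted on an earlier result.

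Recruitment began in April 2018, so the change cannot help patients already dosed. For them, establish whether pre-dose serum was stored. Where it was not, report the pair as missing and do not substitute a local result.

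The cost is a wording amendment and two extra tubes, with storage or processing, for each patient who uses the waiver. Table 3 already schedules both tests at selection for everyone, and the sample size does not change.
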